## Methods

### Design

To examine the differential effects of mindfulness and positive fantasizing in rMDD and ND participants, we designed an open-label intervention cross-over study in which participants received both a mindfulness- and fantasizing intervention, in randomized order. The study is conducted at the University Medical Center Groningen, the Netherlands. The study includes five phases after an initial screening that is used to determine study eligibility. Eligible participants undergo 1) an assessment of baseline characteristics using self-report questionnaires (T0); 2) pre-intervention measurement 1 including one week of baseline momentary measures using Experience Sampling Methods (ESM) ten times per day, cognitive task performance two times per day, 24-h measurements of impedance cardiography (ICG)/electrocardiogram (ECG), one-week actigraphy measurements and an EEG lab measurement and questionnaires in the lab (T1); 3) peri-intervention measurement 1 where participants practice daily with an intervention and undergo the same measurements as in pre-intervention measurement 1 (T2); 3) pre-intervention measurement 2, which takes place after a wash-out period of at least one month consisting of one-week momentary measures, two-times daily cognitive task performance, actigraphy, 24-h of ICG/ECG, and EEG measurements and questionnaires in the lab (T3); 4) peri-intervention measurement 2, including practicing with the not-yet-performed intervention and the same measurements as in pre-intervention measurement 2 (T4). An overview of the study design can be found in Fig. 1.

**Fig. 1 Fig1:**
[figure not shown]
Flowchart of the MINDCOG study

### In- and exclusion criteria

#### Inclusion criteria

In order to be eligible to participate in this study, all participants must meet all the following criteria:Participants should be between 18 and 60 years old. They should not exceed 60 years of age in order to minimize aging-related decline in information processing [45];Participants should display normal intelligence (IQ > 85, as assessed with the Dutch Adult Reading Test (DART) [46] and/or having finished an education on at least vocational level) in order to assure sufficient task comprehension.

Participants in the rMDD group should meet the following criteria to make sure that they are at high risk of depressive relapse and currently show no clinically relevant severity of depressive symptoms:Remitted participants should have experienced at least two depressive episodes, according to criteria defined by the Diagnostic Statistical Manual, version 5 (DSM-5), experienced in past ten years;Remitted participants should score 21 or lower on the Inventory of Depressive Symptomatology - Self-Report (IDS-SR30) [47], indicative of the absence of clinically relevant depressive symptoms.

#### Exclusion criteria

Furthermore, individuals who meet any of the following criteria are excluded from participation in this study:Fulfilling criteria for any current DSM-5 diagnosis as objectified with the Structured Clinical Interview for DSM-5 (SCID-5) [48];Daily use of anti-depressive medication, benzodiazepines, methylphenidate, beta blockers or other medication potentially influencing ICG/ECG currently or in the last four weeks;Recent engagement (defined as in their last episode, or as one year prior to inclusion in case the last episode was more than a year before inclusion) in PCT including the positive fantasizing technique and/or have recent experiences (defined as daily practice in the past two years for at least two weeks) with mindfulness, meditation, or mindful yoga. This criterion prevents underestimation of true effects of the interventions and maximizes treatment effects;Participation in another clinical intervention study at the moment of inclusion in the study to prevent overlapping intervention effects.

Individuals for the ND control group who additionally meet any of the following criteria are excluded from participation in this study:Presence of symptoms of depression according to the IDS-SR30 (score > 13), to make sure they are not currently experiencing clinically relevant depressive symptoms;Any life-time psychopathology of any disorder as objectified with the SCID-5.

### Sample size

To our knowledge, we are the first to combine ESM, ICG/ECG measures, and laboratory EEG measures to study the effects of different interventions on PC. It is difficult to do power calculations for our study since there is no software available that can make predictions for our chosen statistical methods (linear mixed effect models & generalized additive models; see Statistical Analyses). We therefore calculated the sample sizes using G*Power (version 3.1.9.4) for t-tests based on questionnaire measures.

In order to study the differential effects between mindfulness and positive fantasizing on PC in individuals vulnerable for depressive relapse, we will include 50 rMDD participants. In a meta-analytic review, Perestelo-Perez et al. [49] compared the effects of Mindfulness-Based Cognitive Therapy with usual care on rumination in patients with a current depressive disorder or a depressive disorder in the past. They observed a Hedges’ *g* of -0.59 for the effect of Mindfulness-Based Cognitive Therapy compared to usual care in reducing ruminative thinking. Using G*Power 3.1.9.4, sample sizes based on these outcomes were calculated. We expect PC to reduce after mindfulness and positive fantasizing. Therefore the sample size for one-tailed t-tests was calculated. To conduct one-tailed t-tests with a statistical power of 80%, the sample size should be *n* = 36 participants. A sample size of *n* = 50 rMDD participants should therefore give sufficient power to draw reliable conclusions about treatment effects, especially since questionnaires are a less sensitive measure than most of the other measurements used in the current study (i.e., ESM, ICG/ECG and laboratory EEG). This relatively large sample size also helps us to buffer against inevitable data losses related to e.g., participants not completing all questionnaires or technical malfunctions of the physiological measurements.

To conduct reliable between-group comparisons on how the effects of mindfulness and fantasizing on PC differ between rMDD and ND individuals, we will include 50 ND participants that are matched to the 50 rMDD participants on age, sex, and education level. In a study of Lois and Wessa [50], they compared self-reported rumination scores between rMDD individuals and matched healthy controls at a baseline level. They observed a t-value of *t*(48) = 2.4 (effect size Cohen’s *d* = 0.686) comparing rumination scores between rMDD participants and controls. Based on these outcomes, sample sizes were calculated using G*Power 3.1.9.4. No specific direction of effects was hypothesized for the effects of mindfulness and fantasizing on PC in rMDD versus ND individuals. Therefore, the sample size for two-tailed t-tests was calculated. To conduct two-tailed t-tests with a statistical power of 80%, sample sizes should be *n* = 28 participants per group. This suggests a sample size of *n* = 50 participants per group should give sufficient power to draw reliable conclusions about between-group differences in changes in PC.

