## Statistical analyses

### Study aim 1

To test whether psychological and psychophysiological indices of PC are differentially affected by fantasizing vs. mindfulness, we will examine within-subject changes in pre- and peri-intervention measurements in the dynamics and content of self-reported PC, HR and HRV during self-reported PC, and electrophysiological correlates of PC and compare those between the fantasizing and mindfulness condition. We will check whether the relationships are linear or nonlinear. If the relationships are linear, we will perform linear mixed effect models (LME). If the relationships are non-linear, we will perform generalized additive models (GAMs) [71].

To examine changes in the dynamics and content of self-reported PC after interventions, several variables of PC over time will be examined. Specifically, we will consider rumination, occurrence of off-task thinking, valence of thoughts, temporal orientation of thoughts, self-relatedness of thoughts, and stickiness of thoughts. If interventions differently affect these variables of PC, we expect to find an interaction effect between intervention (fantasizing or mindfulness), session (pre- or peri-intervention), and time (time of ESM beep). For example, we hypothesized that mindfulness increases the frequency of present thoughts (i.e., temporal orientation of thought) in contrast to fantasizing where we do not expect this. If this would be the case, an interaction effect between intervention, session, and time on the temporal orientation of thoughts would be found. After running the LMEs or GAMs, visualization of the data will be used to further study the dynamics of the different changes over time.

To examine within-subject changes in pre- and peri-intervention measurements on the physiological correlates of PC, we will examine changes in HR and HRV and EEG voltage during self-reported PC. If interventions differently affect these physiological correlates of PC, we expect to find an interaction effect between intervention (fantasizing or mindfulness), session (pre- or peri-intervention), and time (in minutes to milliseconds).

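### The aim 1 sample size of 36 fits a per-group figure for two independent groups, one-tailed, so the 80% power and the data-loss buffer claimed for the single cross-over group of 50 are unsupported

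*Protocol article*

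**What the plan says.** The aim 1 paragraph of the Sample size section opens with the purpose: "In order to study the differential effects between mindfulness and positive fantasizing on PC in individuals vulnerable for depressive relapse, we will include 50 rMDD" (that is, 50 people in remission). Its effect size is a Hedges' g of -0.59 from a meta-analytic review, "for the effect of Mindfulness-Based Cognitive Therapy compared to usual care in reducing ruminative thinking". The choice of tail follows from a stated expectation: "We expect PC to reduce after mindfulness and positive fantasizing". The next sentence reads "Therefore the sample size for one-tailed t-tests was calculated". The result is then given in these words: "To conduct one-tailed t-tests with a statistical power of 80%, the sample size should be" 36. The paragraph concludes that 50 remitted participants give sufficient power and that the larger number also protects against lost data.

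The next paragraph sizes the comparison of remitted with never-depressed people. Because no direction was hypothesised there, "Therefore, the sample size for two-tailed t-tests was calculated", and that result is labelled as a number per group. The aim 1 result carries no such label.

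Under Statistical analyses, Study aim 1, if the techniques act differently "we expect to find an interaction effect between intervention (fantasizing or mindfulness), session (pre- or peri-intervention), and time (time of ESM beep"). The general threshold is p < 0.05 with Benjamini–Hochberg correction, and no one-sided test is mentioned.

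**The concern.** Aim 1 is a within-person comparison: the Background and Design sections describe a cross-over in which each participant receives both techniques. No two independent groups exist for this aim. If 36 came from an independent-groups routine, it is a number per arm and cannot be set directly against a single group of 50.

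The tail is a second problem. An expected fall after each technique is a pre-to-peri direction common to both. It says nothing about which technique lowers perseverative cognition more, yet that difference is what the paragraph sets out to size.

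Two statements rest on 36: that 50 is sufficient, and that the excess covers data loss. If 36 does not belong to this comparison, a null aim 1 result would be read against a sensitivity that was never established.

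**Working it through.** **Inputs.** From the Sample size section: effect 0.59 in absolute value, power 80%, one tail, n = 36, planned n = 50. The section gives no alpha; 0.05 is assumed, in line with the general threshold under Statistical analyses. The within-person correlation r is not stated and is varied below.

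**Step 1: reproduce 36.** The method is the exact noncentral t. For independent groups with n per group, the noncentrality is d × √(n/2) with 2n − 2 degrees of freedom. For a one-sample or paired test it is d × √n with n − 1 degrees of freedom. With d = 0.59:

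| Test | n for 80% power | Power at n = 36 |
|---|---|---|
| Independent groups, one-tailed | 37 per group | 79.8% (36 per group) |
| Independent groups, two-tailed | 47 per group | 69.5% (36 per group) |
| One-sample or paired, one-tailed | 20 | 96.6% |
| One-sample or paired, two-tailed | 25 | 93.1% |

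Only the first row comes within one participant of 36. The normal approximation gives exactly 36 per group, as does exact t with the effect rounded to 0.60. Read as a total for two groups of 18, 36 would give 53.6% power one-tailed.

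**Step 2: compare with the article's own figure for the same effect.** The section on COVID-19 changes uses d = 0.59 from another study, a one-sample t-test and 80% power, and reports n = 20. That equals the third row. The article thus gives 20 and 36 for the same standardised effect and power. A difference in routine (one-sample versus independent groups) accounts for this.

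**Step 3: the planned comparison, as an illustration.** For each participant, take the difference in change: (mindfulness peri minus pre) less (fantasizing peri minus pre). With equal between-person SD σ and equal correlation r across the four weekly means, its variance is 4σ²(1 − r). If the techniques differed by 0.59σ, the standardised effect would be dz = 0.59 / (2√(1 − r)). Example at r = 0.5: 0.59 / (2 × 0.7071) = 0.417. Two-sided, alpha 0.05:

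| r | dz | n for 80% power | Power at 36 | Power at 50 |
|---|---|---|---|---|
| 0.3 | 0.353 | 66 | 54% | 69% |
| 0.5 | 0.417 | 48 | 68% | 82% |
| 0.6 | 0.466 | 39 | 78% | 90% |
| 0.7 | 0.539 | 30 | 88% | 96% |

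Under this model 36 is enough only from r of about 0.63 upwards.

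**Step 4: the favourable reading.** If 0.59 were itself the paired standardised effect, 25 would suffice two-sided, and 50 would give 98%.

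**The case against.** The article does not name the t-test type, so the routine is inferred, and exact t gives 37 rather than 36. That is fair. The match is to within one participant, but no other standard variant at 0.59 comes near.

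If the only slip is independent versus paired, it is conservative: 25 would do and 50 would be ample. This stands, and it rules out a reading that a reader might infer, namely that the trial is underpowered. The documents do not support it. Even in the difference-in-change illustration, 50 gives 82% at r = 0.5.

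A reader might also infer that the plan fixes a two-sided test for aim 1. It does not say so. Two-sidedness is inferred from an interaction test at p < 0.05 with no one-sided test stated. Some component hypotheses are directional, such as more present-focused thought under mindfulness than under fantasizing, and one tail would be coherent for a fall within each technique. But the paragraph is about the difference between techniques, and the reason it gives for one tail does not bear on that difference.

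A reader might likewise infer that the buffer mostly or wholly disappears. That depends on r, which is not stated: at r = 0.7 only 30 are needed. The buffer of 14 is itself only the subtraction 50 − 36; the article gives no number.

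Finally, the article says openly that t-tests on questionnaires stand in for mixed and additive models. That excuses a gap between proxy and model. It does not excuse a proxy whose design and tail do not fit the comparison it is named for.

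**Conclusion.** The point holds as one about support, not about adequacy. The figure of 36 is almost certainly a per-group number for independent groups, one-tailed. Set against one cross-over group of 50, it supports neither 80% power at 36 nor a buffer above 36 for the difference between techniques.

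How far the true requirement lies from 36 cannot be settled from the article. It ranges from 25, if 0.59 is the paired effect, to 66, if 0.59 is a difference in between-person SD units and r = 0.3. The matching power at 50 ranges from 98% to 69%. The illustration assumes alpha 0.05 two-sided, equal correlation across four weeks, and a between-technique difference as large as the cited effect against usual care, which the article does not claim. It leaves out the time term of the interaction and the multiplicity correction.

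**What to change.** Replace the n = 36 sentence with a within-person calculation for the difference in change between the techniques. Make it two-sided unless a direction between the techniques is justified. State alpha, the assumed difference and the assumed r, and report the power of 50 participants over a range of r, with the expected data loss set against that result.

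If 36 is kept, label it as per group, independent groups, one-tailed, and do not base the buffer on it.

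The cost is a short recalculation and a change of wording. Enrolment, data collection and analysis stay as they are. The drawback is that the stated margin may become less favourable.

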For all analyses, we will use a critical *p*-value of *p* < 0.05 that will be corrected for multiple comparisons using the Benjamini–Hochberg procedure [72]. Analyses will be performed using the statistical software R*.* LMEs and GAMs allow not only fixed effects, but also random effects. Random effects such as individual variability will therefore be added as well. In case non-significant effect are found for the LME analyses, Bayes Factors will be computed to find out whether this non-significant effect can be seen as proof for the H0 hypotheses (null effects) or whether this is due to the lack of reliability in the collected data [73]. Calculating Bayes Factors is not possible for GAMs, so this will only be conducted for LME models.

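### The aim 2 figure of 28 per group does not follow from its stated two-tailed inputs (35 does), and a baseline difference in rumination cannot support the power claim about changes in PC

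*Protocol article*

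**What the plan says.** The Sample size section of the protocol article bases the aim 2 calculation on an earlier study that "compared self-reported rumination scores between rMDD individuals and matched healthy controls at a baseline level". It reports the result as follows: "They observed a t-value of *t*(48) = 2.4 (effect size Cohen’s *d* = 0.686) comparing rumination scores between rMDD participants and controls". Because no direction was hypothesised for the group comparison, the article continues: "Therefore, the sample size for two-tailed t-tests was calculated". The result is given as "To conduct two-tailed t-tests with a statistical power of 80%, sample sizes should be *n* = 28 participants per group".

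The planned number is larger: "we will include 50 ND participants that are matched to the 50 rMDD participants on age, sex, and education level". From this the section concludes that 50 per group "should give sufficient power to draw reliable conclusions about between-group differences in changes in PC".

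The Sample size section does not restate alpha. The Statistical analyses section sets it: "For all analyses, we will use a critical *p*-value of *p* < 0.05", with a Benjamini-Hochberg correction for multiple comparisons. The aim 2 outcomes are group differences in the change from pre- to peri-intervention, and the aim 2 analysis looks for an interaction of group, session and intervention.

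**The concern.** There are two separate faults in one paragraph.

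- **The number.** Effect size, sidedness, power and alpha are all fixed by the article, and together they do not give 28.
- **The inference.** The effect size describes how far the two groups differ in rumination before any intervention. The closing sentence uses it to vouch for power on how differently the groups change. A difference in level carries no information about the size of a difference in change, or about the standard deviation of the change.

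At stake is how an aim 2 result will be read. A reader who accepts the closing sentence may take a null group comparison as good evidence that the groups respond alike, although no power for that comparison has been shown.

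**Working it through.** **Inputs**

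- d = 0.686, two independent groups, two-tailed, 80% power, planned n = 50 per group (Sample size).
- Alpha = 0.05 (Statistical analyses).

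**Formula.** With n per group, df = 2n − 2 and noncentrality δ = d·√(n/2). Two-tailed power is P(T > c) + P(T < −c), where T is noncentral t with df and δ, and c is the 97.5% point of the central t. This is the exact t-test calculation.

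**Check of alpha and method against the article's other two-tailed two-group calculation.** The section on COVID-19 related changes gives 19 per group for d = 0.96 at 80% power. At alpha 0.05, n = 18 gives 79.9% and n = 19 gives 82.1%. The stated 19 reproduces exactly, so alpha 0.05 and this method fit the article's practice.

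**The same calculation for d = 0.686, two-tailed**

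| n per group | df | c | δ | Power |
|---|---|---|---|---|
| 28 | 54 | 2.005 | 0.686 × √14 = 2.567 | 71.3% |
| 34 | 66 | 1.997 | 0.686 × √17 = 2.828 | 79.6% |
| 35 | 68 | 1.995 | 0.686 × √17.5 = 2.870 | 80.8% |
| 50 | 98 | 1.984 | 0.686 × √25 = 3.430 | 92.5% |

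The requirement is 35 per group, which is 7 (25%) more than 28. The normal approximation gives 2 × (1.960 + 0.842)² / 0.686² = 33.4, so 34, which is also not 28.

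**Does rounding of d explain it?** From t = 2.4 with 48 df, d is 2.4 × √(2/25) = 0.679 if the groups were 25 each, or 2 × 2.4/√48 = 0.693 by the other common conversion. For these values and 0.686, the two-tailed requirement runs from 34 to 36. Rounding does not explain 28.

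**Where 28 might come from.** A one-tailed test at alpha 0.05 needs 27 with d = 0.686 (power 80.0%) and 28 with d = 0.68 or 0.679. A two-tailed test at 70% power needs exactly 28 with d = 0.686. Neither matches the stated inputs, and the article does not say which, if either, was run.

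**What 50 per group delivers for a change score.** Treat each participant's change as one value and compare two groups of 50 with a two-tailed t-test at unadjusted alpha 0.05. Power of 80% is reached at a difference of 0.566 SD of the change score (δ = 0.566 × 5 = 2.83, power 80.0%). The article gives no expected difference in change. For assumed differences of 0.3, 0.4 and 0.5 SD, power is 32%, 51% and 70%.

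**The case against.** The strongest reply is that nothing in the trial depends on 28. The study plans 50 per group, which exceeds 35 and gives about 92% power for the stated effect. This stands. The article puts no figure on its margin, and the error does not make the planned sample too small for the contrast that was calculated.

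The second reply is that the article is open about its approach. It says the comparison was made at baseline, that power for the planned mixed and additive models could not be calculated, and that t-tests on questionnaire measures served instead. This stands in part. The source of d is disclosed and a t-test is a fair simplification. But a t-test on change scores was equally available, and the disclosure does not bridge the step from a difference in level to a claim about change.

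Some stronger readings are tempting and should be resisted:

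- A reader might infer that 28 is a one-tailed result mislabelled as two-tailed. That is possible but unproven: the stated d gives 27 one-tailed, and another setting gives 28 exactly.
- A reader might try to put a power on the three-way interaction, or carry d = 0.686 over to the 25 per group in the physiological phase. The first needs a difference in change and a correlation between the two changes, and the article gives neither. The second ignores the separate calculation that the article makes for those outcomes, with its own effect sizes.
- A reader might apply alpha 0.05/6 for the six PC variables. That is a Bonferroni threshold, whereas the article specifies Benjamini-Hochberg.

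**Conclusion.** The point holds in two parts of unequal weight.

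1. **Arithmetic, minor.** The stated 28 per group should be 35, and 28 gives about 71% power. This follows from the article's own inputs. It rests on alpha 0.05, which the article states for all analyses and which its d = 0.96 calculation confirms.
2. **Unsupported conclusion, the part that matters.** Correcting 28 to 35 would not rescue the closing sentence, because d = 0.686 concerns baseline level and aim 2 concerns change. What 50 per group supports is 80% power for a group difference of about 0.57 SD in a change score. That figure assumes one change score per participant, complete data and no multiplicity correction. The planned models use repeated measurements, so their power may differ from this figure.

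A reader might infer that the trial is too small for aim 2. The documents do not support that: they give no expected difference in change, so adequacy is neither shown nor refuted.

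**What to change.** In the Sample size section:

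- Replace 28 per group with 35 per group for the two-tailed calculation with d = 0.686.
- Replace the closing sentence. Say that 50 per group gives about 92% power for the baseline contrast. Then say that, under the same t-test simplification, it gives 80% two-tailed power at unadjusted alpha 0.05 for a between-group difference of about 0.57 SD in a change score.
- Add that this is before the Benjamini-Hochberg correction and that no power has been shown for the group by session by intervention interaction.

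This is a change of text only. Recruitment, design and analysis stay as they are. The downside is a less favourable power statement for aim 2.
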